Appendix C: Demographic Interview

[figure not shown]

[figure not shown]

[figure not shown]
Appendix D: Telephone Script and Exit Interview

**Interviewer Instruction**: Intervention Group (Q1-7 for telephone follow-up at weeks 2 and 4, as well at exit interview at week 6); Control Group (Q8 at exit interview at week 6 ONLY)

[Thank the subjects for their participation in the study. Remind the subject of the study design and the plan to have a total of three calls, 2, 4 and 6 weeks]. Explain the purpose of the call: To evaluate frequency of practice –based on their diary (not memory) – and to identify barriers to daily practice. Confirm that they have their diary with them during the call.]

1. *How many times in the last two weeks have you practiced the complete audio (from beginning to end)?*
2. *On the days when you did not practice the entire audio CD, how many times did you start the audio but were unable to finish? [if >1, as them to ‘list’ the reasons for not completing]*
3. *On the days when you were not able to practice, please tell me what prevented you from practicing*
4. *Did you have any problems or issues when you were practicing?*
5. *In general, on a scale of 1 to 10, with one being not motivated and 10 being very motivated, how motivated were you to practice in the last 2 weeks?*
6. *In general, on a scale of 1 to 10, with one being not very confident and 10 being very confident, how confident are you that you will continue to practice?*
7. *Is there anything you would like to tell us about your experiences with your practice, or do you have any questions of us?*

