All participants will receive usual care education (UCE), which includes transplant specific information for the recipient and the caregiver, as well as caregiver resources. After study enrollment, caregiver subjects will be randomized to either the control group or the intervention group. A permuted block randomization with allocation ratio of 1:1 will be performed by the study statistician. All participants will meet 1:1 with a study investigator to review the UCE materials. Participants in the intervention group will also receive an audio recording of a 20 minute yoga-based stress reduction intervention, as well as instructions on how to complete the intervention; they will be asked to practice the twenty minute audio file daily for the six weeks of the intervention. The six-week length of the intervention, as well as the 20 minute time of the audio file, was selected based upon the length of similar interventions in other caregiver populations, with interventions ranging between four to ten weeks [^37^](#_ENREF_37)^,^[^43^](#_ENREF_43). All study visits will be scheduled around the HSCT recipient’s schedule and visits to minimize burden for the caregiver. The initial visit for all participants will occur prior to the patient’s initial discharge from the hospital and within 7 days of the HSCT infusion (Day 0+7). Subjects in the intervention group will receive a brief phone call at weeks two and four (+/- 7 days) to assess progress and to record practice. All subjects will participate in an exit interview at week six (+/- 7 days). Study questionnaires will be administered to all subjects at baseline and again at week six (+/- 7 days). Completion will take approximately 20 minutes through a web-based system. If the electronic system is unavailable, a hard copy of the questionnaires will be available for completion. Caregivers in either group who complete baseline assessments but are no longer able to return to the clinical center for their week 6 study visit will be given the option to complete the week 6 questionnaires electronically.

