# 9.0 REPORTING PROCEDURES

Adverse events, Protocol deviations (PDs), Unanticipated problems (UP), and serious adverse events (SAEs), are defined in NIH HRPP SOP 16 (“Reporting Requirements for Unanticipated Problems, Adverse Events and Protocol Deviations.”). All adverse events occurring during the study, including those observed by or reported to the research team, will be recorded. Serious UPs, and serious PDs, will be reported to the IRB and Clinical Director as soon as possible but not more than 7 days after the PI first learns of the event. Not serious UPs will be reported to the IRB and Clinical Director as soon as possible but not more than 14 days after the PI first learns of the event. Not serious PDs will be reported to the IRB as soon as possible but not more than 14 days after the PI first learns of the event. In addition, SAEs that do not meet the criteria of UP will be reported to the IRB Chair and Clinical Director within 14 days of learning of the event using the SAE form in PTMS.

Expected or non-serious adverse events will be reported at the time of continuing review and are defined in section 9.1. The principal investigator will provide continuous, close monitoring of data and side effects, and adverse events to identify trends. The principal investigator will be responsible for revising the protocol as needed to maintain safety.

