## 9.1 Adverse Events

Adverse events reported under this protocol will be limited to those events which are possibly, probably or definitely related to the research described in this protocol. An serious adverse event is defined as any untoward medical occurrences that 1) result in death, 2) are life-threatening, 3) require hospitalization, 4) cause persistent or significant disability /incapacity, 5) result in congenital anomalies or birth defects, 6) are other conditions which in the judgment of the investigators represent significant hazards. All serious adverse events will be reported to the IRB within 7 days for death or life threatening adverse event and within 15 days for all others.

The principal investigator will report events to the IRB promptly in accordance with NIH Human Research Protection Program Standard Operating Procedure #16 (Reporting Requirements for Unanticipated Problems, Adverse Events and Protocol Deviations). The principal investigator will provide continuous, close monitoring of data and side effects and adverse events to identify trends. The principal investigator will be responsible for revising the protocol as needed to maintain safety. The IRB will review adverse events annually at time of continuing review to also evaluate trends and will require follow up plans from the principal investigator whenever a trend is identified.

The anticipated adverse consequences of participation in this protocol are the inconvenience of time required for study procedures (i.e. stress reduction intervention practice), venipuncture, possible emotional distress related to questions that relate to the affective state of the subject, and minor muscle soreness or strain from the intervention. Because of the gentle nature of the intervention, it is unlikely to cause any adverse events.

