**Exit Interview ONLY:**

1. *At the beginning of the study you received information on caregiver resources at the NIH Clinical Center (e.g. We Care Web site). Did you access that link or any other caregiver resources since the start of the study? If so, please describe.*

[Thank the subjects again for their participation in the study.]

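### Appendix D prompts only the intervention arm about problems, and no printed question common to both arms asks about adverse events

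*Protocol*

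**What the plan says.** Protocol Section 9.0 sets a broad recording rule: "All adverse events occurring during the study, including those observed by or reported to the research team, will be recorded". The principal investigator is to watch these data for trends. Section 9.1 narrows what is reported, though not what is recorded: "Adverse events reported under this protocol will be limited to those events which are possibly, probably or definitely related to the research". Its list of anticipated consequences includes "venipuncture, possible emotional distress related to questions that relate to the affective state of the subject", as well as muscle soreness or strain from the yoga.

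The printed questions are in Appendix D. For one arm the instruction is "Intervention Group (Q1-7 for telephone follow-up at weeks 2 and 4, as well at exit interview at week 6"; for the other it is "Control Group (Q8 at exit interview at week 6 ONLY". Q4 reads "Did you have any problems or issues when you were practicing". Q2 and Q3 ask why a session was not finished or not done, and Q7 is open-ended. The item under the exit-interview heading, which is the control arm's question, asks "Did you access that link or any other caregiver resources since the start of the study".

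Section 3.0 restricts interim contact to one arm: "Subjects in the intervention group will receive a brief phone call at weeks two and four (+/- 7 days". Controls have no scheduled contact between the baseline visit and week 6.

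**The concern.** The recording rule covers both arms, but the scripted prompts reach only one. A control caregiver with a sore arm after a blood draw, or upset by the questionnaires, enters the record only if staff notice it or the caregiver volunteers it. An intervention caregiver has three scripted occasions to mention a problem, plus an open question each time.

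If events are then tabulated by arm, part of any excess under yoga would reflect how often people were asked. The question is about data collection and is fixed in the protocol, so a statistical analysis plan cannot settle it later: events that were never elicited cannot be recovered in analysis.

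**Working it through.** The protocol gives no figure to reproduce. The check counts scripted prompts and sets them against the recording rule and the other contacts available.

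**1. Prompts by arm** (Section 3.0, Figure 3, Section 5.5, Appendix D)

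| | Intervention | Control |
|---|---|---|
| Scheduled contacts after baseline | 3 (weeks 2, 4, 6) | 1 (week 6) |
| Occasions with Q4 on problems | 3 | 0 |
| Other items able to elicit an event | Q2, Q3, Q7 at each contact | none |

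With 39 per arm (Section 6.1) and no attrition, Q4 is put 39 x 3 = 117 times in the intervention arm and 39 x 0 = 0 times in the control arm.

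**2. Anticipated harms against the script** (Section 9.1, Appendix D)

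- Soreness or strain from yoga: within the scope of Q4, intervention arm only, as is appropriate.
- Venipuncture problems: possible in both arms; no scripted question in either.
- Distress from the questionnaires: possible in both arms; no scripted question in either.

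The gap is therefore partly shared. Q4 is confined to problems while practising, so the intervention arm has no general adverse-event question either.

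**3. Other week-6 contacts**

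- Section 10.4 lists a second visit with blood collection, a clinic visit and surveys.
- The Precis has a physical assessment repeated at the end of the six weeks for all participants. Figure 3 marks the clinical assessment at baseline only. These two disagree.
- Figure 3 repeats the demographic interview at week 6, but the Appendix C form is not shown in the copy reviewed.
- Appendix B says the exit interview will address non-treatment effects and that medications and life events will be collected. The printed control item covers neither.
- Section 3.0 lets caregivers who cannot return complete the week-6 questionnaires electronically, which removes the chance of observation in person.

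Events can surface at these contacts, but none of them is described as asking about adverse events.

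**4. How unequal asking could show in counts (illustration only; p and s are assumed)**

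Expected recorded events = n x p x s, where n = 39, p is the same true risk in both arms, and s is the share captured. Take s = 0.9 when asked and s = 0.2 to 0.5 when events must be volunteered.

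| p | Intervention | Control |
|---|---|---|
| 0.10 | 39 x 0.10 x 0.9 = 3.51 | 0.78 to 1.95 |
| 0.20 | 39 x 0.20 x 0.9 = 7.02 | 1.56 to 3.90 |
| 0.30 | 39 x 0.30 x 0.9 = 10.53 | 2.34 to 5.85 |

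The ratio does not depend on p: 0.9/0.5 = 1.8 to 0.9/0.2 = 4.5. Because Q4 covers practice only, 0.9 is generous for complaints in general. If the prompts caught no more than would be volunteered, the two values of s would be equal and the ratio would be 1. A range of 1 to 4.5 under these assumptions shows the likely direction, not the size.

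**The case against.** Appendix D is mainly an adherence script: its stated purpose is to measure how often people practise and what prevents them. Controls have no practice to ask about, so some asymmetry is natural. The recording rule also covers observed and reported events and does not demand solicitation. Blood is drawn by trained staff, an investigator is available during online questionnaires (Section 10.2), and anxiety and depression are measured in both arms at both time points. No objective in Section 1 and no analysis in Section 6.2 compares harms between arms, and Section 10.2 puts the study at no more than minimal risk.

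Most of this stands, and it rules out several stronger readings that a reader might infer:

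- That controls are never asked about problems. This cannot be shown: the Appendix C form is not visible, and the Precis places a physical assessment at week 6 for everyone.
- That the recording rule cannot be met. Volunteered and observed events can meet it in part; what is missing is a stated means of eliciting events.
- That Q4 is the only item able to bring out an event. Q2, Q3 and Q7 can do so too.
- That complaints would appear only in the yoga arm, or with a definite several-fold excess. That needs capture rates the protocol does not give, and high capture of all complaints does not fit Q4's restriction to practice.

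The objection does not supply a question that both arms are asked. The purpose of the script explains the asymmetry but does not provide another instrument for adverse events.

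**Conclusion.** The point holds in limited form and is minor. Scripted prompting is unequal, at three occasions against none, and no printed question common to both arms asks about adverse events. The rule that all events are recorded thus has no stated solicitation method behind it. Any counts by arm would carry ascertainment bias, probably towards more recorded events under yoga, and the protocol does not allow its size to be estimated. Because no between-arm comparison of harms is planned, no stated analysis fails; what suffers is the completeness of the record and the reading of any trend.

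This rests on Appendix D as printed being the full script, and on the forms not shown containing no adverse-event question. If such a question exists there for both arms, citing it in the protocol would largely settle the matter.

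**What to change.** - Add to the Appendix D week-6 exit interview one neutral adverse-event question, worded identically for all subjects, on any new or worsened health problem or distress since the baseline visit, whether or not linked to practice. Ask it by phone of caregivers who complete week 6 off-site.
- Change the interviewer instruction so that controls answer Q8 plus this question.
- Base any event summary by arm on this question alone, and list events arising from the intervention-only Q1-7 responses separately.
- Reconcile Figure 3 with the Precis on whether the physical assessment is repeated at week 6.

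The cost is a minor amendment and one extra question at an interview both arms already have. The downside is a few more non-serious events to log.

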**Exit Interview ONLY:**

1. *At the beginning of the study you received information on caregiver resources at the NIH Clinical Center (e.g. We Care Web site). Did you access that link or any other caregiver resources since the start of the study? If so, please describe.*

[Thank the subjects again for their participation in the study.]

